##### Focus Groups

When enough participants have been recruited to ensure data collection using interviews is complete, the process will be repeated for recruitment to the focus groups until 10 patients have taken part, at which point recruitment will cease.

#### Clinicians

##### Interviews

In total, 15 clinicians will be recruited in three different ways:

Via the research active clinics assisting with patient recruitment.At the bimonthly GM strategic clinical network for diabetes meeting.At the launch event for the DMW system.

In each of the above settings, a member of the research team will identify key clinicians who are aware of DMW and are engaging with or are likely to engage with patients who are using or have been offered the intervention. The researcher will provide the clinician with a participant information sheet and obtain consent to contact. After a minimum period of 24 hours, the researcher will contact the clinician, ensure that they have understood the participant information, answer any questions relating to the research and then arrange a time, date, and location for the interview to take place. When interviews have been conducted with 15 clinicians or data saturation is reached, this process will end, and we will begin recruitment to the focus groups.

##### Focus Groups

When enough participants have been recruited to ensure data collection using interviews is complete, the process will be repeated for recruitment to the focus groups until 10 patients have taken part, at which point recruitment will cease.

#### Informed Consent

Informed consent will be obtained from all participants by an experienced member of the research team immediately before the interview or focus group taking place, at which point participants will have the opportunity to ask further questions about the study. For face-to-face interviews and focus groups, written consent will be obtained. For telephone interviews, the researcher will read aloud the consent form and consent will be provided verbally over the telephone. This exchange will be audio recorded and later transcribed by an independent company, providing a record of the consent process.

#### Analysis

Data will be analyzed thematically using template analysis [41]. A distinct feature of template analysis is the structured development of a hierarchically organized coding template. This coding template is initially developed based on subset of data (eg, a selection of transcripts that incorporate a range of accounts—in this work, this will allow for analysis of interview data to be undertaken while data collection remains ongoing), then applied to further data and revised and refined as necessary. Codes are organized into meaningful clusters (including hierarchical relationships between codes in a cluster and lateral relationships across clusters) and a full thematic structure developed iteratively.

A further feature of template analysis is that it permits the use of *a priori* themes—themes that are identified in advance of coding as likely helpful or relevant to the analysis but which are understood as tentative and may be refined or discarded if they do not prove to be useful or appropriate. As in previous work that used the constructs of a theoretical model as *a priori* themes to facilitate initial coding [42], in this work (reflecting our particular research aims), the constructs of the TFA [23] will be drawn on as *a priori* themes to initially focus our coding.

We will use established quality-checking procedures, including critical scrutiny and constant comparison of coding. Two researchers will independently code a subset of interviews, discuss to reach consensus, and generate a first version coding template, encompassing both *a priori* and emerging themes. Once the provisional coding template is discussed and agreed, the researchers will then independently apply the coding template to further data in blocks of 5 interviews, then again meet to similarly discuss and reach full consensus. This iterative process will produce a final version template encompassing all relevant materials, which will then be applied to the full data set. At each stage of the analysis, the full research team will check the validity and consistency of coding and agree upon the final thematic framework. An audit trail will be kept, and the staged analysis process will ensure both coding and interpretation are regularly cross-checked.

### Process Evaluation

In collaboration with the digital intervention provider teams, the study team will provide a narrative report on the following observed experiences and outcomes:

The process through which the study was designed.Explore whether the interventions were delivered in line with original plans.Explore whether governance arrangements for the intervention were effective and why.Explore whether the partnership of NHS with innovator firms worked as intended and why.Explore whether the innovator partnerships resulted in improved technology use.Explore whether the NHS has received better products or processes as a result of collaboration, testing, or learning.Explore any benefits to innovation partners of being part of the Test Bed program.Explore whether engagement by each party to the partnership been sufficient and why.Describe any changes made during implementation to ensure effective delivery of the intervention and why these were made.Explore barriers and facilitators to effective delivery (and uptake of technology or services) and how were they overcome or ensured.Report any unintended consequences that needed to be managed and how this was done.Explore scalability of the intervention.

### Patient and Public Involvement

DMW has had patients involved in every stage of the design, prototyping, development, implementation, and review phases of the intervention. The company receives regular feedback from patients via email, secure messaging, and web-based surveys to ensure that the intervention is genuinely patient-centered and holds regular steering group meetings, including representation by patients. In addition, all new product development work involves users. This is usually conducted through design workshops and user prototype testing in the field. Early feedback (and ongoing feedback on rollout) continues to drive changes in the DMW product range. Furthermore, our partner services engage in ongoing dialogue with its users. A person living with diabetes will be enrolled in the study steering group.

*Oviva* Diabetes Support conducts patient and public involvement through its continuous patient feedback via surveys, which is reviewed monthly, and changes to the intervention are made as appropriate.

*Changing Health* sends out feedback surveys to all users at baseline and subsequently every 3 months. The data from these surveys are used to identify potential issues and to continually refine their programs. In addition to this formal channel, *Changing Health* also has a presence on social media (Facebook and Twitter) through which they share user stories and original content of interest to the public.

### Dissemination

We will take the following steps to ensure that results are useful to the NHS and the global clinical community: *ensure effective dissemination of results, such as* (1) deliver conference presentations; (2) peer-review publications; (3) run an engagement workshop on *digital solutions to improve diabetes self-management,* which will involve senior clinicians, NHS England, public health staff, diabetes charities, academics, patients, and the general public; (4) social media postings; and (5) give radio and television interviews and p*resent the results in ways that create maximum utility for clinical users (*eg, clearly describe the practical steps necessary to introduce the system). Participants will be provided with a summary of the main study findings through the DMW website.

## Results

As of May 10, 2021, a total of 316 participants have been recruited for the quantitative study and have successfully enrolled. A total of 278 participants attempted to register but did not have appropriate permissions set by the GPs to gain access to their data. A total of 10 participants have been recruited for the qualitative study (7 practitioners and 3 patients). An extension to recruitment has been granted for the quantitative element of the research, and analysis should be complete by June 2022. Recruitment and analysis for the qualitative study should be complete by June 2021.

## Discussion

### Principal Findings

The GM DMW project seeks to implement innovative solutions to clinical and system-wide challenges in learning and self-management in T2D. The overall aim of the intervention is to deliver optimized clinical care, and the electronic provision of patients’ medical information to patients and practitioners in a timely and accessible way should contribute to achieving this aim. Patients currently struggle to effectively self-manage, and clinicians are limited by not having all relevant information in a unified care record. Furthermore, there is major variation in the level of knowledge that patients have about their diabetes, major variation in the quality of diabetes care across general practices in GM, and major practical and financial challenges in delivering behavioral interventions that support healthier lifestyles and major blocks in clinical care because of diabetes-related psychological distress. These factors are all compounded by low clinic and structured education attendance rates in some patient groups.

There is a clear need to improve patients’ ability to self-manage T2D, and the DMW electronic platform offers an accessible alternative to the current, mostly unsuccessful method of traditional classroom-style education. DMW has been proven popular with patients and practitioners in Scotland; however, uptake across Scotland has been ≈13% (in 2020), with disproportionately lower use in older populations, lower socioeconomic groups, and minority ethnic groups and risks perpetuating or augmenting health inequalities [8]. Exploring issues around the acceptability of the implementation of DMW in GM with both patients and practitioners could offer important insights into possible reasons for the lack of engagement and uptake in certain populations. The findings from this study can be used both to further develop and enhance the DMW system and to improve accessibility and usability in more deprived populations, thus improving equity in access to support for T2D self-management.

If the evaluation demonstrates that DMW and the linked digital behavioral interventions (Oviva and Changing Health) can improve self-management and risk factor levels in people with T2D, then this could lead to a step-change in diabetes management across the NHS and wider. If the economic analysis shows cost savings compared with traditional care, then this would lead to global changes in health care delivery. Therefore, the clinical, psychological, social, economic, and health care resource benefits observed through this application could have a global reach. Furthermore, other adjunct offerings could impact clinical outcomes. If MyCognition improves psychological health in people with T2D, then these data could be used to promote this approach being rolled out across the NHS, which could reduce the huge public health burden of psychological illness associated with T2D.

### Strengths and Limitations

The main strength of the qualitative study is that we will draw on the experience of a wide range of stakeholders with the aim of capturing the most diverse possible range of perspectives to inform the development of DMW and improve the overall number of patients choosing to engage with the intervention.

One of the limitations of the study is that we will not be recruiting patients who do not understand written English. This may result in a biased patient sample, which is not representative of the diverse population of GM, where an estimated 200 different languages are spoken. However, this may provide a topic for future research. Another limitation is that the study will not formally evaluate the influence of digital exclusion on study outcomes. We anticipate differences in digital literacy and the factors that influence this between participants and controls. However, our matching process, followed by multivariable regression that controls for clinically important covariates not included in the matching process, may help to reduce the influence of digital exclusion. We expect that the results of the qualitative work may provide further insights into the role that digital exclusion might have in the results.

### Conclusions

Exploring the acceptability of DMW will provide valuable insight into how stakeholders engage with the intervention and how to improve implementation and uptake within diverse populations. It will compliment a larger body of quantitative research on efficacy, generated by the wider GM Test Bed study and the mixed methods Scottish research [7,8]. By using the TFA [23], an evidence-based framework for researching the acceptability of complex interventions, we will also add to a wider body of evidence around the utility of this tool and increase the transparency and replicability of our findings.

If the use of DMW by patients with diabetes has major clinical, societal, and economic benefits, this will be a global stimulus for research in this area. Researchers and health care managers will be interested in the context in which the interventions were delivered (patients and health care system) and the methods of implementation adopted in the Test Bed. The research will have implications for pharmaceutical companies and other companies involved in producing treatments, interventions, and digital interventions in diabetes care.

This study has multiple potential impacts. In 2011, diabetes consumed 10% (£10 billion; US $13.25 billion) of the NHS budget, and when indirect costs were included (mortality data, sickness data, loss of productivity, and informal care), the cost was estimated at £23 billion (US $30.47 billion). If digital interventions have only a small impact on the self-management of T2D and its complications, then the absolute economic benefits may still be large. The largest cost of managing diabetes comes from the cost of managing its complications. If interventions targeting the management of cardiovascular risk (DMW and behavioral interventions primarily) are successful, then this could have major financial benefits in the United Kingdom and globally.

The treatment of T2D is central to the government’s 2011 National Service Framework (NSF) for diabetes. Our research addresses key NSF standards. The NSF standard 4 states the following:

All adults with diabetes will receive high-quality care...to optimise the control of their blood glucose, blood pressure and other risk factors for developing the complications of diabetes.

If our research shows the expected outcomes, then we will work with leading figures in the Department of Health, Public Health England, NHS England, and NICE to ensure that future policies and guidance include appropriate reference to our work. This project also maps to the aims of (1) the NHS 10-year plan (2019), (2) the NHS England Digital Health Strategy, (3) the National Information Board Personalised Health and Care 2020 plan, and (4) the *State of the Nation* report (2016) produced by Diabetes UK.

Digital interventions have the potential to transform the self-management of T2D and deliver major clinical, psychological, and economic benefits. This Test Bed project aims to assess the impact of a range of digital interventions delivered through DMW in an ethnically and socially diverse group of people with T2D across GM.

### Note on the COVID-19 Pandemic

The plans in relation to the study participants have not been modified because of the COVID-19 pandemic. We expected digital interventions to be effective in improving self-care. However, in the context of the COVID-19 pandemic, it is clear that digital interventions could be even more valuable to people with diabetes because access to face-to-face primary care interventions for people with T2D has been extremely limited and may remain so for many months.

Before the pandemic, the study team was in contact with NHS Digital to obtain data on control participants through the Data Access Request Service. The COVID-19 pandemic provided an alternative route to obtaining these data from NHS Digital through a notice under Regulation 3 (4) of the National Health Service (Control of Patient Information Regulations) 2002. This regulation requires NHS Digital to share confidential patient information with organizations entitled to process this under Control of Patient Information Regulations for COVID-19 purposes.

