#### Outcomes

##### Overview

The primary outcomes will be intervention-related changes compared with changes observed in a matched group of controls, and the secondary outcomes will be within-person intervention-related changes (Textbox 3).

Primary and secondary outcomes.

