**MyCognition**
Primary outcomeChange in diabetes distress score [32-34].Secondary outcomesChange in cognition scores.Changes in referral rates for traditional psychological interventions compared with controls and within-person changes.

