### Analysis

#### Overview

First, the generalizability and relevance of the intervention in the context of GM will be assessed. We will descriptively compare participants in the interventions to other populations: those who did not participate, the population of GM, and the population of England. For the comparison to those who did not take up the intervention, we will use data on age, sex, ethnicity, residence location socioeconomic deprivation quintile (2019 Index of Multiple Deprivation) and risk factors (from their electronic record) for a comparison with the participants. For the GM and England comparisons, we will compare patients based on age, sex, risk factors, and comorbidities using data sourced from NHS Digital.

Second, we will examine engagement with the intervention (as quantified by relevant metrics in the app, eg, visits and time spent), and descriptively assess how it varies across age groups, sex, ethnic groups (South Asian, Black, mixed, White, and other populations) and socioeconomic deprivation quintiles. A multiple linear regression model will be used to more formally evaluate the association between the variables listed above (age, sex, ethnicity, and socioeconomic deprivation) and engagement.

Third, we will aim to use quasi-experimental methods to evaluate the effectiveness of the intervention on each outcome by comparing prospective changes in outcomes between matched participants and controls and by performing pre- versus postintervention comparisons in participants only. Matching will be performed using the caliper method, which is a modification of the nearest neighbor matching procedure that imposes a tolerance on the difference in cohort characteristics [37]. Here, we will combine calipers relating to age range (+2 or −2 years) and with exact match of gender, ethnicity, and general practice. In the matched group approach, participants receiving the interventions will be randomly matched to nonparticipants on age, sex, ethnicity, and general practice (as a proxy for socioeconomic deprivation).

Where there are differences between participants and controls in relation to matched characteristics or other characteristics such as prevalent cardiovascular disease, we will include these variables as covariates regression models.

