In the presence of time series data, we will use an interrupted time series design for each outcome of interest, which takes into account the preintervention trends of the outcome as well as the information on controls and quantify the effect of the intervention on future outcome levels. If only 2 time points are available (eg, before and after the intervention), we will use a simple linear regression model with clustered errors or a paired 2-tailed *t* test to compare means in each outcome at the 2 time points.

For example, for the main outcome, change in HbA_1c_ levels, we will compare changes from baseline (defined as April 1, 2016, to July 1, 2019) during the intervention period (July 1, 2019, to March 31, 2022) in matched participants and controls after adjusting for clinically significant differences in baseline weight, blood pressure, cholesterol, creatinine, cardiovascular disease, and smoking.

If the numbers of cases and controls are large, we will explore effect heterogeneity in subgroup analyses (as separate models or using interaction terms in the main models described above) by ethnicity, age groups, socioeconomic deprivation quintile, cognitive function (assessed by MyCognition), and level of engagement with digital interventions.

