### Economic Evaluation

#### Short-term Health Benefits and Consequences to Costs

In the short term, economic evaluation will focus on the cost-effectiveness of DMW measured over the intervention period (up to December 2020). Data on changes in outcomes from the quantitative evaluation, such as HbA_1c_ levels, will be compared against costs across population groups. Relevant costs will be direct NHS costs assessed from intervention-related costs and changes in routine health care use, as assessed from rates of primary care consultations and hospital attendance during the observation period. The unit costs of delivering traditional face-to-face behavior change interventions and psychological interventions are available in GM, enabling meaningful cost comparisons. Further unit costs will be sources of NHS reference costs and the unit costs of health and social care.

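### Participants-only before/after changes in health care use and referrals are labelled intervention-related although they probably span the pandemic, and the short-term cost comparison names no comparator

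*Protocol article*

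**What the plan says.** The Abstract, Aims and Objectives, and the Outcomes overview all rank two contrasts. The primary one compares change in participants with change in matched controls. For the other, "the secondary outcomes will be within-person intervention-related changes". The Analysis overview applies both to each outcome; the second is done "by performing pre- versus postintervention comparisons in participants only".

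The outcomes include health care use (clinic and hospital attendance, medication) for Diabetes My Way (DMW), Oviva and Changing Health. For MyCognition, Textbox 3 lists "Changes in referral rates for traditional psychological interventions compared with controls and within-person changes".

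The only worked example of the time windows is for HbA1c: "baseline (defined as April 1, 2016, to July 1, 2019", against outcomes "during the intervention period (July 1, 2019, to March 31, 2022". The section on duration of data access describes the same split for risk factors such as HbA1c and blood pressure.

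The short-term economic evaluation draws on intervention costs and on "changes in routine health care use, as assessed from rates of primary care consultations and hospital attendance during the observation period". It names no comparator for that change, and it gives the intervention period as ending in December 2020.

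The note on the pandemic says "The plans in relation to the study participants have not been modified because of the COVID-19 pandemic". It goes on to say that "access to face-to-face primary care interventions for people with T2D has been extremely limited and may remain so for many months", and uses this to argue that digital support may be worth more. It does not discuss what the restriction does to a before/after comparison.

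**The concern.** Attendance and referral counts depend directly on how much service is on offer. The article itself says that supply fell sharply. A comparison of the same people before and after has no means of telling that fall from an effect of the intervention, so *intervention-related* is a causal label that this estimate cannot carry. The Design section uses the same term for changes adjusted for those seen in matched cohorts, so one label covers two quite different quantities.

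If an intervention did nothing, its users could still show fewer clinic visits, hospital attendances and referrals, and the secondary analysis would present this under a causal name. The article gives no rule for reading the two contrasts when they disagree. With only two time points, one of the permitted methods is a paired t test, which uses no controls.

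Costs matter too because the Discussion attaches wide consequences to a finding of savings against traditional care. The wording that feeds that finding should leave no room for an uncontrolled estimate.

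**Working it through.** The article gives no numerical target for health care use, referrals or costs, so there is no stated figure to reproduce. The check is one of calendar overlap.

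**Inputs from the article**
- Baseline window: 1 April 2016 to 1 July 2019, which is 9 + 12 + 12 + 6 = 39 months (HbA1c example in the Analysis section).
- Intervention window: 1 July 2019 to 31 March 2022, which is 6 + 12 + 12 + 3 = 33 months (same place). The Introduction gives the roll-out as August 2019 to March 2022, which is 32 months.
- Economic window: to December 2020. Counted from July 2019 this is 6 + 12 = 18 months.

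**Assumptions, because the article gives no figure**
- The pandemic restrictions start in March 2020; range January to July 2020.
- The 2016 to 2019 baseline is also used for health care use and referrals.
- Use falls by the same fraction in everyone during pandemic months; 20% to 40% is used for illustration.

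**Overlap = pandemic months in the window / months in the window**
- Baseline: 0/39 = 0% for any start in 2020.
- Intervention period: 25/33 = 76%. January start: 27/33 = 82%. July start: 21/33 = 64%.
- Counted from August 2019: 25/32 = 78% (21/32 = 66% to 27/32 = 84%).
- Economic window: 10/18 = 56%. January start: 12/18 = 67%. July start: 6/18 = 33%.

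**Apparent within-person change with no true effect = −overlap × assumed fall**
- Full intervention period: 0.76 × 20% = 15% and 0.76 × 40% = 30%, both as reductions. Assumed falls of 10% and 50% give 8% and 38%.
- Economic window, if costs rested on before/after use: 0.56 × 20% = 11% and 0.56 × 40% = 22%.

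**The same calculation against matched controls**
- If controls lose the same fraction over the same months, the difference in relative change is 0. Controls are matched on general practice, among other things, which makes a shared fall in primary care supply plausible. A fall that differs between DMW users and people who declined it would remain.

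The overlap figures follow from the article's dates and the assumed start. The sizes of the apparent reductions rest wholly on the assumed fall in use.

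**The case against.** The strongest reply is that the remedy is already in the plan. The matched comparison is primary and applies to each outcome, referral rates are expressly compared with controls, and the interrupted time series uses control information. Service-use data for controls are requested over the same calendar period, which makes sense only if use is to be compared. All of this stands, and it confines the problem to the secondary contrast.

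A reader might infer that the study will report the pandemic fall in care as a saving due to DMW. The article does not support that. The short-term economic section is silent on the comparator for changes in use; it does not state a before/after design. It also draws on results of the quantitative evaluation, whose primary estimates are controlled, and on unit costs of traditional services. The long-term section compares quality-adjusted life years with the control group. Nor should the 76% overlap be carried over to costs, whose stated window is shorter. Referral rates are an outcome of MyCognition and not of DMW.

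Two further limits stand. The 2016 to 2019 baseline is stated for HbA1c and risk factors, not for attendance or referrals. Enrolment ran over time, so a contrast anchored on each person's enrolment date would put pandemic months on both sides for late joiners. Also, the note speaks of face-to-face primary care; it says nothing of hospital attendance.

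It could be added that a condensed article may leave detail to a fuller plan. That does not answer the point that remains: the article itself fixes the causal label, fixes the participants-only analysis, and states that nothing was changed.

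**Conclusion.** The concern holds for the secondary within-person analyses of health care use and, for MyCognition, referral rates. As written, they carry a causal label that they cannot support, and the article acknowledges the disturbance without guarding this contrast against it. If the HbA1c baseline also serves these outcomes, a wholly pre-pandemic period is compared with one that is about 76% pandemic (64% to 82%), given an assumed start in March 2020 (July back to January 2020). A 20% to 40% general fall, also assumed, would then appear as a 15% to 30% reduction with no true effect.

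The primary matched-control contrast is not affected by a fall that both groups share.

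For costs there is an open risk: no comparator is named, and the window is about 56% pandemic (33% to 67%). Separately, the economic section's December 2020 end contradicts the March 2022 end given in the Introduction and the Analysis section. These dates must be reconciled.

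This is a moderate correction to a secondary analysis. It does not undermine the primary result.

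**What to change.** - For health care use, referral rates and costs, make the participant-minus-matched-control difference in change, over the same calendar months, the only estimate of effect or saving.
- In the short-term economic section, name that comparator for the change in routine health care use, and reconcile the December 2020 end date with March 2022.
- Keep within-person changes as descriptive summaries, and remove *intervention-related* from their label in the Abstract, Aims and Objectives, and the Outcomes overview.

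The cost is mainly wording plus a little analysis, since clinic and hospital attendance for controls is already requested for the same period. Two things are given up or need work. Within-person results can no longer be reported as effects. Referral data for controls must also be confirmed as available, because the listed control data items do not name them.
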